### 2.10. Intervention

Upon consenting to participate, patients will be randomized into two study arms based on the intervention administered:Control Group: Patients will receive modifications to their pharmacological treatment alongside standard nutritional recommendations. The control group will follow a Mediterranean diet with increased caloric and protein intake during the acute flare. The diet will emphasize a balanced nutritional intake without unnecessary food restrictions, along with adequate fiber and hydration (as tolerated), and a reduction in ultra-processed food consumption.Experimental Group: Patients will receive modifications to their pharmacological treatment and will be assigned to an intervention consisting of an exclusion diet in conjunction with supplemental enteral nutrition. This nutritional strategy will involve a progressive increase in the caloric intake derived from the diet, coupled with a corresponding reduction in supplemental enteral nutrition.

Prior to initiating the nutritional intervention—and subsequently at 6 and 12 weeks after the onset of the diet—alterations in body composition and functionality will be evaluated through anthropometric measurements and biochemical parameters pertinent to both the underlying pathology and the overall health status of the patient. Comprehensive functional assessments, including dynamometry and additional analyses such as BIA and nutritional ultrasound, will be conducted. Furthermore, a detailed nutritional and morphofunctional evaluation will be performed 24 and 48 weeks after the initiation of the exclusion diet [Figure 1].

Baseline biological samples (blood, urine, and stool specimens) will be collected before the start of the nutritional intervention. During the intervention, additional collections will occur at the 6-, 12-, 24-week visits, with a final sample collection at 48 weeks. A detailed assessment schedule can be found in Table 1.

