### 2.12. Randomization and Blinding

Patients will be randomized in a 1:1 ratio after meeting the study inclusion and exclusion criteria. In the control group, patients will receive standard nutritional recommendations, whereas in the intervention group, they will follow a dietary strategy based on partial enteral nutrition combined with an exclusion diet, which has been shown to be effective in inducing remission, promoting mucosal healing, and serving as a rescue therapy for patients with inadequate response to biologic treatments.

Patients in the intervention group will be required to maintain this dietary strategy for 12 weeks, with structured follow-up visits at 6, 12, 24, and 48 weeks. Subsequently, patients should continue with the maintenance phase starting from week 13 onwards. Nutritional intake will be adjusted to ensure a balanced provision of macronutrients and essential micronutrients, prioritizing the inclusion of key substrates for short-chain fatty acid production while avoiding foods and additives with potential pro-inflammatory effects.

Simple randomization will be computer-generated and conducted by a member of the research team at the study site. Due to the nature of the intervention, neither patients nor research or medical staff will be blinded. Group assignment will be disclosed to patients at the moment of their participation acceptance.

Furthermore, to minimize the risk of bias, the clinicians from the Gastroenterology Department responsible for performing imaging assessments, as well as the translational researchers from the Biomedical Research Institute of Murcia (IMIB) in charge of analyzing blood, urine, and stool samples, will remain blinded to the dietary allocation of the study participants.

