### 2.13. Data and Sample Collection and Analysis of Variables

#### 2.13.1. Data Collection

Data and biological sample collection will be conducted prior to the initiation of the nutritional intervention (baseline) and throughout the intervention during scheduled follow-up visits at 6, 12, 24, and 48 weeks. A comprehensive clinical assessment will be performed, encompassing the collection of anthropometric data (height, weight, body mass index), detailed records of patient medication, and evaluation of dietary intake using a 24 h dietary recall and Food Frequency Questionnaires (FFQs). Additionally, validated instruments will be employed to assess quality of life (CVEII-9) [Figure 2] and physical activity levels (IPAQ) [Figure 3].

The use of Mediterranean diet adherence questionnaires (PREDIMED) [Figure 4], the 24 h dietary record, and Food Frequency Questionnaires (FFQs) are useful tools for assessing adherence to the Mediterranean diet. However, they are not without limitations, as they may not capture inter-individual variability in diet or may be misinterpreted by subjects. Measurement of certain biomarkers that increase during a Mediterranean diet (such as carotenoids, n-3 fatty acids, and/or monounsaturated fatty acids) may be a more objective alternative to assess dietary adherence [13].

Body composition and functional changes will be analyzed using biochemical parameters associated with the underlying pathology and the patient’s general health status. Functional performance tests, including dynamometry, BIA, and nutritional ultrasonography, will be conducted to evaluate morphofunctional alterations. A comprehensive nutritional and morphofunctional assessment will be repeated three months following the conclusion of the dietary intervention.

Clinical remission will be evaluated using the Harvey–Bradshaw Activity Index (score < 5) and fecal calprotectin levels (<250 µg/g). At weeks 24 and 48, the radiological imaging study performed at baseline (e.g., MRI enterography or intestinal ultrasonography) will be repeated and/or an intestinal biopsy may be performed to objectively confirm remission of CD.

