**Assessments**						
Quality of life questionnaire (CVEII-9)		X	X	X	X	X
Harvey–Bradshaw activity index		X	X	X	X	X
Physical activity questionnaire (PAQ)		X			X	X
Food Frequency Questionnaire (FFQ)		X			X	X
24 h dietary recall		X	X	X	X	X
Mediterranean diet adherence questionnaire (PREDIMED)			X		X	X
Anthropometry (weight, height, BMI)		X		X	X	X
Sarcopenia screening (SARC-F)		X		X	X	X
Functional sarcopenia tests (dynamometry)		X		X	X	X
Bioelectrical Impedance Analysis (BIA)		X	X	X	X	X
Nutritional ultrasound		X		X	X	X
Blood tests, urine and stool samples		X	X	X	X	X
Intestinal imaging (MRI/intestinal ultrasound).		X			X	X
Intestinal biopsy. Optional.		X			X	X

Pre-DE: before diet exclusion. t0: baseline or initial visit. t1 (6 w): visit at 6 weeks. t2 (12 w): visit at 6 weeks. t3 (24 w): visit at 24 weeks. t4 (48 w): visit at 48 weeks.

**Table 2 jcm-14-03998-t002:** Obligatory, permitted, and prohibited foods in the exclusion diet in patients with Crohn’s disease.

Phase	Type of Food	
Phase 1 (0–6 weeks)	Obligatory	Protein-rich foods: fresh chicken breast (at least 150–200 g/day), 2 eggs/day. Carbohydrate-rich foods: 2 fresh potatoes/day peeled, cooked and cooled before consumption, 2 bananas/day, 1 apple/day peeled.
	Permitted	Protein-rich foods: 100–150 g of fresh white fish once a week as a substitute for chicken. Carbohydrate-rich foods: white rice (unlimited), rice noodles without preservatives (unlimited), rice flour for baking (unlimited). Fruits: 1 avocado/day (no more 1/2 avocado per meal), 5 ripe strawberries/day, 1 cantaloupe slice/day. Vegetables: 2 tomatoes/day (or 6 cherry tomatoes), 2 cucumbers/day peeled, 1 carrot/day, fresh spinach (225 g raw leaves/day), 3 lettuce leaves once a day. Condiments: olive oil, canola oil, salt, pepper, paprika, cinnamon, cumin, turmeric, mint, oregano, coriander, rosemary, sage, basil, thyme, dill, parsley, onion (all types), garlic, ginger, natural lemon juice, honey (3 tbsp/day), sugar (3 teaspoons/day). Drinks: water, sparkling water, infusions, 1 glass of freshly squeezed orange juice per day.

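### Table 1 gives PREDIMED no baseline and no week-12 assessment, so the score's change from baseline and its value at the end of the 12-week phase cannot be obtained

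*Protocol article*

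**What the plan says.** Section 2.10 sets the comparator: "The control group will follow a Mediterranean diet with increased caloric and protein intake during the acute flare". Section 2.12 sets the length of the required diet in the other arm: "Patients in the intervention group will be required to maintain this dietary strategy for 12 weeks", with a maintenance phase from week 13. The Introduction describes that maintenance phase as one in which a Mediterranean diet is encouraged.

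Section 2.13.1 says that PREDIMED, the 24 h dietary record and the FFQ "are useful tools for assessing adherence to the Mediterranean diet", and acknowledges their limits. It gives the general timing of data collection as baseline and "throughout the intervention during scheduled follow-up visits at 6, 12, 24, and 48 weeks". It gives no separate timing for PREDIMED. Section 2.10 refers the reader to Table 1 for the detailed schedule.

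In Table 1, the "Mediterranean diet adherence questionnaire (PREDIMED)" row is marked at 6, 24 and 48 weeks only. The "24 h dietary recall" row is marked at t0 and at all four follow-up visits. The "Food Frequency Questionnaire (FFQ)" row is marked at t0, 24 and 48 weeks. The footnote defines the first columns as "t0: baseline or initial visit. t1 (6 w): visit at 6 weeks".

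**The concern.** PREDIMED is the one instrument in the schedule dedicated to Mediterranean adherence, and a Mediterranean diet is what the control arm is assigned. Without a t0 score, usual adherence before the trial is unknown on this scale. A week-6 or later score then cannot be read as a change, and a patient who already ate this way cannot be told apart from one who took up the advice. The week-6 score is post-randomisation and cannot stand in for a baseline.

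Without a week-12 score, the scale says nothing about the control arm at the end of the 12-week phase. The exclusion-diet arm also has no reference value just before its maintenance phase begins. Patients and staff know the allocation, and the Discussion lists variable adherence as a threat to interpretation, so a documented contrast between the diets is worth having. A baseline score that was not taken cannot be recovered once the diet has started.

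**Working it through.** No sample-size or power figure of the protocol is at issue. The check is a reading of the schedule.

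**1. Is the gap real or an effect of text extraction?** Each of the 14 assessment rows splits into seven fields: one label and six time-point cells (Pre-DE, t0, 6, 12, 24 and 48 weeks). The PREDIMED row also has seven, so its marks have not shifted through a lost cell.

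**2. The diet and activity rows side by side.**

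| Row of Table 1 | t0 | 6 w | 12 w | 24 w | 48 w |
|---|---|---|---|---|---|
| PREDIMED | – | X | – | X | X |
| FFQ | X | – | – | X | X |
| Physical activity questionnaire | X | – | – | X | X |
| 24 h recall | X | X | X | X | X |

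**3. Counts over all 14 rows.**
- Rows without a t0 mark: 1 (PREDIMED). The other 14 − 1 = 13 have one.
- Rows without a week-12 mark: 5 (physical activity questionnaire, FFQ, PREDIMED, intestinal imaging, optional biopsy).

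The missing baseline is therefore unique to PREDIMED. The missing week 12 is not.

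**4. What can and cannot be obtained from this schedule.**
- PREDIMED, change from t0: not obtainable at any visit.
- PREDIMED at week 12: not obtainable.
- PREDIMED, difference between arms at 6, 24 and 48 weeks, and change from week 6 onward: obtainable.
- Diet by 24 h recall: obtainable at t0 and week 12, but each recall describes a single day.
- Diet by FFQ: change from t0 to weeks 24 and 48 obtainable; no value at week 6 or 12.

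**5. Number affected.** Section 2.11 plans at least 50–55 patients per group, so 2 × 50 = 100 to 2 × 55 = 110 in total. Under Table 1 as printed, none would have a t0 or week-12 PREDIMED score.

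**The case against.** Several points on the other side stand.

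- **Other tools cover part of the gap.** A reader might infer that Mediterranean adherence at baseline and week 12 cannot be assessed at all. The documents do not support that. Section 2.13.1 names three tools, and Table 1 schedules the recall at both times and the FFQ at t0. Only the PREDIMED score is missing.
- **PREDIMED does not measure the exclusion diet.** A reader might infer that adherence to the 12-week diet goes unmeasured in the experimental arm because PREDIMED is skipped at week 12. That diet is a different one, so a week-12 score would not show adherence to it. In that arm week 12 matters only as the reference before maintenance. In the control arm, the week-6 score still falls within the 12-week phase.
- **No efficacy endpoint depends on it.** Mediterranean adherence is not among the five specific aims in section 2.1. The article does not name week 12 as a primary time point, and imaging to confirm remission is scheduled at weeks 24 and 48, when PREDIMED is taken.
- **A power argument would be misplaced.** It is tempting to express the loss as detectable differences at 48 per arm with and without baseline adjustment. The protocol states no between-arm PREDIMED hypothesis, and the correlation needed would be an assumption. Randomisation keeps the follow-up comparisons unbiased, so a baseline would add only precision to them.
- **The row may be a slip.** The FFQ and physical activity rows run t0, 24 and 48 weeks, so the week-6 mark could be a misplaced t0 mark. The Table 1 footnote has a slip of its own, describing t2 (12 w) as a 6-week visit. The documents cannot settle this. If it is a slip, correcting the table restores the baseline, but week 12 stays blank.
- **FFQ and physical activity.** Their absence at week 12 might be read as contradicting section 2.13.1. That section gives general visit timing and section 2.10 defers to Table 1 for detail, so taking longer questionnaires less often is an ordinary scheduling choice.

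**Conclusion.** The point holds for the PREDIMED score. Table 1 provides neither a baseline nor a week-12 value, the missing baseline is unique among 14 rows, and the article gives no reason for it. Change from baseline in the score, and its value at the end of the 12-week phase, are unavailable for all 100–110 planned patients. The consequence is a weaker reading of control-arm adherence and of the dietary contrast between arms. It biases no efficacy comparison and removes no stated endpoint. This is a minor but cheap improvement, best made before recruitment because the baseline cannot be collected later.

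The conclusion assumes that sites follow Table 1 as printed and that the 24 h record of section 2.13.1 is the 24 h recall of Table 1.

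**What to change.** In the PREDIMED row of Table 1, add marks at t0 and t2 (12 w) and keep those at 6, 24 and 48 weeks. If the week-6 mark was meant for t0, correct it and still add t2. Use the t0 score as the baseline when PREDIMED is compared between arms. No change to the FFQ or physical activity rows is needed for this point.

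The cost is one short questionnaire at two visits patients already attend, and an edit to one table row. At most this means 2 × 100 = 200 to 2 × 110 = 220 extra questionnaires across the trial, with no added visit, sample or procedure.

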## Data Availability

Not applicable.
